Screening visit: This screening visit will occur at the subjects’ pre-natal visit before or around 18 weeks gestation. The study coordinator at each Clinical Center will obtain the schedules for all prenatal visits for the week, and scheduled visits will be reviewed for potential subjects. During the visit, the Study Coordinator/RA will describe the study, present the potential subject with a written description of the study, and review the eligibility criteria via a screening questionnaire and a study admissions criteria questionnaire. If the subject is eligible, does not meet any exclusion criteria, and expresses interest in the study, the subject will either be enrolled at this visit or an enrollment visit will be scheduled within one month.

Enrollment visit: A separate enrollment/randomization visit will be scheduled within one month of the prenatal visit, but not later than the 18th week of gestation. In some instances, enrollment will occur at the time the subject is screened. At this visit, the Study Coordinator/RA will review the study procedures and consent form. Once subject consent is obtained, the subject will be assigned a Study ID and several questionnaires will be administered, a skin pigmentation test will be performed, and blood will be drawn and stored for 25 (OH) D measurements. After questionnaires have been answered and the subject does not meet any further exclusion

criteria, the subject will be randomized to one of the treatment arms (see Section VII.C. for details of randomization).

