#### **P.2.a. Plan for *Specific Aim 1***

The hypothesis that the incidence of asthma and recurrent wheeze at age three years is reduced in the high-dose Vitamin D supplementation group will be tested using logistic regression, allowing for fixed effects of center. Additional analyses will consider the modification of vitamin D exposure effects by maternal and child demographic/behavioral factors such as maternal age, BMI and weight gain during pregnancy, maternal history of asthma/allergy, and other factors potentially associated with asthma and/or vitamin D exposure. The variables to be considered are summarized in Table 3. For variables that are measured post-natally, recall bias is a potential confounder among parents of infants diagnosed with asthma. However, the prospective nature of the data collection should limit the extent of this and other potential sources of bias. Due to the design of this clinical trial, we expect that the randomization process will distribute these variables equally between the intervention and control groups. However, we will check the distribution of these variables prior to conducting the analyses, and will adjust for variables that may be unevenly distributed across treatment and control groups.

**Table 3. Information on selected potential confounders of the relationship between 25(OH)D levels and asthma/recurrent wheeze in 3-yr old children**

|                                  |                                                                                 |
|----------------------------------|---------------------------------------------------------------------------------|
| Prenatal variables               | Socioeconomic status                                                            |
|                                  | Maternal diet                                                                   |
|                                  | Maternal sun exposure behavior                                                  |
|                                  | Maternal age and parity                                                         |
|                                  | Maternal history of asthma and allergies                                        |
|                                  | Maternal pre-pregnancy BMI and weight gain in pregnancy                         |
|                                  | Maternal medication use in pregnancy (antibiotics, acetaminophen, NSAIDs, etc.) |

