where  $x_i$  denotes an indicator function for level of vitamin D supplementation (0=400 IU, 1=4400 IU) in the  $i^{\text{th}}$  subject, while  $a_{1,i}$  and  $a_{2,i}$  are indicator functions for study center. The specific aim for this outcome tests the hypothesis that  $\beta=0$ , asthma and recurrent wheeze incidence do not significantly differ across treatment groups, after adjusting for the potential effects of study center heterogeneity.

To assess modification of vitamin D exposure levels by other demographic and/or behavioral variables, the model is:

$$\text{logit Pr}(M_i = 1 \mid x_i, a_i) = \alpha + \beta x_i + \gamma_1 a_{1,i} + \gamma_2 a_{2,i} + \sum_k \delta_k z_{ki} + \sum_k \eta_k x_i z_{ki}$$

where  $z_{ki}$  represents the  $k$  measured covariates for each subject, and the other variables are as described above. This model addresses two hypotheses. First, main effects testing for behavioral/demographic covariates (Table 3), or the hypothesis that  $\delta_k=0$ , will be used to examine whether maternal age, BMI, or other factors predict asthma and recurrent wheeze risk at age 3. More importantly, inclusion of any significant main effects will adjust for any distributional imbalances of these factors across the Vitamin D supplemented and placebo

groups. Second, this model tests the hypothesis that  $\eta_k=0$ , or whether any maternal, child, or demographic/behavioral covariates modify the relationship between vitamin D intake and our primary outcome. To obtain a parsimonious model and limit multiple testing, only covariates with significant main effects and strong biologic plausibility for an exposure-dependent impact on asthma/recurrent wheeze risk will be considered for interaction testing with Vitamin D supplementation status. For example, only the prenatal and some delivery variables (e.g., gestational age, birthweight, length) listed in Table 3 will be considered, as the factors modifying the impact of Vitamin D supplementation on asthma and/or recurrent wheeze should occur temporally (i.e. in utero).

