#### **P.2.c Plan for Specific Aim 3**

Incidence of allergy, doctor's diagnosis of eczema, and lower respiratory tract infection (LRI) at age 3 will be individually assessed. Like asthma and recurrent wheeze, two of the three secondary outcomes are dichotomous endpoints, and will be analyzed using logistic regression. For allergy, logistic regression will be used for specific IgE and linear regression will be used for log transformed total serum IgE level. Both a primary analysis of the relationship between vitamin D and the secondary outcome of interest will be conducted, as well as additional analyses including demographic and environmental risk factors for allergy, eczema, and LRI. The primary analysis, as well as additional analyses testing main demographic/behavioral effects and effect modification, will be conducted along the lines of analyses described for Specific Aim 2. The covariates to be considered for main effects and interaction analyses will be identical to those outlined for Specific Aim 2.

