#### **P.2.d. Plan for Specific Aim 4**

This specific aim investigates the immediate and long-term impact of vitamin D supplementation on circulating 25(OH)D blood levels. The immediate impact of Vitamin D on 25(OH)D will be assessed through maternal plasma and cord blood measurements taken at delivery. The long-term influence will be examined via longitudinal analyses using children's blood measurements obtained at ages 1 and 3.

The hypotheses that 25(OH)D levels in maternal plasma and cord blood will be higher in the 4400 IU group will be tested using standard linear regression. If necessary, 25(OH)D levels will be transformed to meet the distributional requirements for the analysis. The 25(OH)D levels in maternal plasma and cord blood will be treated as separate outcomes, although both testing procedures for each analysis will be similar and are described jointly below. As with specific aims 1 and 2, the primary analysis will examine the relationship between 25(OH)D and vitamin D levels, while the secondary analysis will include other important demographic and

environmental factors related to 25(OH)D levels, such as climate and dietary vitamin D intake, testing for main effects and effect modification for these factors.

Letting  $y_i$  denote the 25(OH)D levels for each subject (as measured in mother's plasma for the first hypothesis, and cord blood for the second hypothesis), the model for the primary analysis is:

$$y_i = \alpha + \beta x_i + \gamma_1 a_{1,i} + \gamma_2 a_{2,i} + \varepsilon_i$$

where the covariates and parameters are as defined in Specific Aim 1. However, Specific Aim 3 tests the hypothesis that  $\beta=0$ , 25(OH)D levels do not significantly differ across the Vitamin D supplemented and control groups. All relevant covariates listed in Table 3 will be considered for the final model. For example, covariates measured post-natally would not be considered for inclusion in the analysis of maternal plasma or cord blood at delivery. Additionally, factors known to be directly associated with OH(25)D levels (i.e. sun exposure behavior, diet, ethnicity), will be included in the final model even if they are not statistically significant predictors of circulating vitamin D levels.

To assess modification of 25(OH)D levels by other demographic and behavioral variables, the model is:

$$y_i = \alpha + \beta x_i + \gamma_1 a_{1,i} + \gamma_2 a_{2,i} + \sum_k \delta_k Z_{ki} + \sum_k \eta_k x_i Z_{ki} + \varepsilon_i$$

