where the parameters are as defined in Specific Aim 1. The  $k$  measured covariates for these analyses will be environmental, maternal, and child factors specific to 25(OH)D levels, such as sun exposure behavior, dietary intake of Vitamin D, and ethnicity. Additionally, any relevant covariates from Table 9 demonstrating main effects that have biologically plausible interactions with Vitamin D supplementation will be tested for effect modification. For both models, it is assumed that  $\varepsilon_i \sim N(0, \sigma^2)$ . The hypothesis that  $\delta_k=0$  will be used to examine whether any of these factors predict 25(OH)D levels, and the results will be used to adjust for any distributional imbalances of these factors across Vitamin D supplementation groups. As with the previous specific aims, we will also tests for effect modification via the hypothesis that  $\eta_k=0$ , or whether any maternal, child, or demographic/environmental covariates modify the relationship between vitamin D intake and circulating 25(OH)D levels in mother's plasma or cord blood. Additionally, we will follow the guidelines outlined in Specific Aim 2 to obtain the most parsimonious model.

The hypothesis that 25(OH)D levels in the child's blood will be higher in the 4400 IU group at birth, age 1 and age 3 will be tested using a repeated measures analysis framework such as generalized estimating equations.

#### P.2.d. Plan for Specific Aim 5

This specific aim investigates whether sufficient vitamin D supplementation in the pregnant mother is associated with reduced incidence of preterm birth (birth <37 weeks gestation) and/or preeclampsia, gestational hypertension, and/or HELLP syndrome compared to a usual care control group in VDAART.

The hypothesis that the incidence of preterm birth/preeclampsia, gestational hypertension and HELLP syndrome (PB/PE) is reduced in the high-dose vitamin D supplementation will be tested using logistic regression, allowing for fixed effect of center. Additional analysis will consider the modification of vitamin D exposure effects by maternal demographic/behavioral factors such as maternal age, BMI and weight gain during pregnancy, and maternal history of asthma/allergy, race, and other factors potentially associated with preterm birth/preeclampsia, gestational hypertension, HELLP or vitamin D exposure.

Letting  $M_i$  be an indicator function for the primary endpoint, PB/PE, for the  $i^{\text{th}}$  subject, the model is:

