## **C. Randomization and Treatment Assignment**

Participants who consent and are deemed eligible to participate will be randomized by the Data Coordinating Center (DCC) to either of the 2 arms of the trial and will be sequentially assigned a six-digit Study Identification Number (Study ID). The first digit of the Study ID will identify the site (St. Louis, San Diego, or Boston) and the next four digits will identify the participant; and the last digit will be a check digit that is calculated from a formula to ensure the accuracy of data entry. Only those who indicate their intention to follow-up until the child is 3 years old will be randomized. Randomization will be performed prior to enrollment of any study participants by the DCC using a system that automates the random assignment of treatment groups to Study ID numbers. The randomization scheme will employ permuted blocks, and one blocked allocation list per stratum (study site and racial/ethnic group) will be generated. That is, separate permuted block randomization lists will be maintained for each racial/ethnic group – White/Non-Hispanics, White/Hispanic, Black (including Hispanic Black), and Other – within each study site. This will ensure that within each site, there is approximate balance across arms over the course of enrollment, and that within ethnic groups within site, there is also approximately

equal representation on both arms. A woman who is deemed eligible will receive the next available Study ID number for her given study center site and ethnic group. The Study ID will be linked to the women's Screening ID. It should be noted that women who are deemed ineligible will not receive Study IDs (i.e. randomization to a treatment). This will help ensure balance in treatment and control groups by not 'wasting' randomization assignments on ineligible subjects.

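### The primary models for Aims 1 and 5 adjust for centre only, although randomisation is stratified by site and race/ethnicity (minor)

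*Supplement*

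**What the plan says.** Current Protocol, section VII.C: "one blocked allocation list per stratum (study site and racial/ethnic group) will be generated". Section C.1 then gives a rule that places every woman in one of four groups for this purpose. With three sites that makes 12 strata.

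Section P.2.a (Aim 1): the primary hypothesis "will be tested using logistic regression, allowing for fixed effects of center". The model equation has an intercept, the arm indicator and two centre indicators, and the test of the arm coefficient is made "after adjusting for the potential effects of study center heterogeneity". For anything further, the plan "will adjust for variables that may be unevenly distributed across treatment and control groups"; the candidates are in Table 3, which does not list race or ethnicity.

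The Aim 5 plan (the second section numbered P.2.d) has the same form: its hypothesis "will be tested using logistic regression, allowing for fixed effect of center". Race appears there only among possible effect modifiers.

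Section P.2.c (Aim 3): the analyses "will be conducted along the lines of analyses described for Specific Aim 2", with the same covariates. Aim 2 is now the maternal 25(OH)D plan (P.2.b).

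Aim 4 treats ethnicity differently: "factors known to be directly associated with OH(25)D levels (i.e. sun exposure behavior, diet, ethnicity), will be included in the final model", whether or not it is significant, and its primary equation already has the centre indicators.

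The Addendum to Analysis Plan brings in interval-censored time-to-event analyses but states no stratification factor or covariate for them.

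**The concern.** When allocation is balanced within strata that predict the outcome, a model that leaves those strata out uses a standard error slightly larger than the true sampling variability. The test is then conservative and some power is given away. The plan's only route for adding race/ethnicity to Aim 1 is a check for imbalance, and blocking within race/ethnicity makes imbalance on that factor unlikely. The rule therefore tends to exclude the one factor that the design singled out besides site.

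The Aim 3 pointer is a separate, textual fault that needs no assumption. The Summary of Protocol Changes records that Aims 1 and 2 changed places (items 3 and 23). P.2.b now has no centre term, no effect-modification model, and covariates chosen for 25(OH)D: sun exposure, age and diet. Read literally, eczema, lower respiratory infection and IgE would be analysed with that plan. The Aim 4 text has the same leftover where it refers to Aim 2 for guidance on a parsimonious model; that guidance now stands under Aim 1.

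**Working it through.** **1. The plan's own power figure.** Inputs from Q.1 and Table 4: 330 per arm, control incidence 50%, 25% relative reduction (37.5%), two-sided 0.05. By the arcsine formula that the protocol names:

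- h = 2·asin(√0.50) − 2·asin(√0.375) = 1.5708 − 1.3181 = 0.2527
- power = Φ(h·√(330/2) − 1.960) = Φ(3.246 − 1.960) = Φ(1.286) = 0.901

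The stated figure is 0.906. The pooled two-proportion formula also gives 0.901. All nine cells of Table 4 agree with these formulas within 0.9 points. The simulation described in Q.1 varies incidence across sites and mentions no variation by race, so the table describes the centre-only analysis.

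**2. What a race/ethnicity term would change.** The documents give no incidence by race and no expected mix. Assumed: mix 30/15/40/15%, and a spread of 0 to 30 points in control incidence across groups. From the protocol: 660 children, three sites of 220, a 10-point spread across sites, 25% reduction. Blocks of four within site by race were assumed. There were 4,000 simulated trials per row, a Wald test at 1.96, and both models were fitted to the same data.

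| Control incidence | Assumed spread | Centre only | Centre + race/ethnicity |
|---|---|---|---|
| 50% | 0 | 0.903 | 0.905 |
| 50% | 10 points | 0.899 | 0.901 |
| 50% | 20 points | 0.907 | 0.912 |
| 50% | 30 points | 0.905 | 0.916 |
| 40% | 0 | 0.787 | 0.788 |
| 40% | 10 points | 0.774 | 0.777 |
| 40% | 20 points | 0.778 | 0.786 |
| 40% | 30 points | 0.785 | 0.801 |

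The gain is about 0.1 to 1.6 points. The Monte Carlo standard error of each entry is 0.5 to 0.7 points; the paired differences are more precise. Interim looks were not simulated.

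**3. Type I error.** In 6,000 null trials per setting at 45% incidence, centre only against centre plus race/ethnicity gave 0.047 against 0.050 at a 20-point spread, and 0.042 against 0.049 at 30 points. The Monte Carlo standard error is 0.3 points, and the zero-spread runs gave 0.058 for both models, so a closed-form check is useful.

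- With the group offsets used in the simulation (−0.5, 0.1, 0.5, 0 times the spread), the between-group variance is 0.1723 × spread².
- The outcome variance after centre is 0.45 × 0.55 − (2/3) × 0.05² = 0.2458.
- 20 points: 0.00689/0.2458 = 0.028. True over model SE = √(1 − 0.028) = 0.986. Type I error = 2·[1 − Φ(1.960/0.986)] = 0.047.
- 30 points: 0.01550/0.2458 = 0.063. The SE ratio is 0.968 and the type I error is 0.043.

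The closed form agrees with the simulation: the test is conservative, and only slightly.

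**4. Baseline 25(OH)D, an optional addition for Aim 4.** At enrolment, "blood will be drawn and stored for 25 (OH) D measurements". In a linear model a baseline covariate with correlation r multiplies the SE by √(1 − r²). For an assumed r of 0.4 to 0.6 this is 0.917 to 0.800, a fall of 8 to 20%. With the Table 7 inputs (SD 40, 330 per arm, two-sided 0.01), SE = 40·√(2/330) = 3.11. Power at 7.5 nmol/L is Φ(7.5/3.11 − 2.576) = 0.43 (stated 0.444), and it rises to 0.52 to 0.67 with the covariate. At the expected 35 nmol/L, 35/3.11 = 11.2, so power is above 0.999 either way.

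**The case against.** The strongest reply is that nothing in the documents shows race/ethnicity to be prognostic for asthma or wheeze. The group mix and the spreads above are assumptions, and even a 30-point spread costs only about 1.6 points of power. A conservative test creates no false-positive risk. All of this stands, and it is why the point is minor.

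Four stronger readings are tempting, and the documents do not support them.

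- **The stated power is too high.** It is not. Table 4 was computed for the centre-only analysis and it reproduces.
- **The odds ratio is biased toward 1.** The mean log odds ratio at 50% incidence and a 30-point spread was −0.517 with centre only and −0.547 with race/ethnicity added. That is non-collapsibility: the two models estimate different conditional odds ratios, and neither is a biased version of the other.
- **Adding baseline 25(OH)D would narrow the Aim 2 interval.** The √(1 − r²) rule is for linear models, and Aim 2 is logistic. Simulating 800 women with means 80 and 115, SD 40, a cut-off of 75 nmol/L and r of 0.4 to 0.6, the SE of the log odds ratio rose by 7 to 19%. The estimate moved outward as well, so the test gained a little. Power for Aim 2 is stated as above 0.999 in every cell regardless.
- **Aim 4 lacks centre and ethnicity.** Its primary equation has centre, and its final model forces ethnicity in.

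On P.2.c, one can fairly say that the intent is clear: Q.3 describes the Aim 3 simulations as like those for the primary outcome, with a centre effect. The pointer is therefore clerical, but the text that governs the analysis is still wrong as written.

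**Conclusion.** The point holds as a mismatch between design and analysis: race/ethnicity defines the allocation lists but is in neither the Aim 1 nor the Aim 5 primary model, and the addendum does not mend this. If race/ethnicity is prognostic, which is an assumption, the centre-only test has a type I error of about 0.047 at a 20-point and 0.042 at a 30-point spread, and gives up about 0.1 to 1.6 points of power over spreads of 0 to 30 points. If it is not prognostic, almost nothing is lost. The validity of the primary test is not in doubt. The main reason to change the plan is that a design factor belongs in the pre-specified model and should not depend on an imbalance check made after the data are in. The stale Aim 3 pointer is a definite error of text. Severity: minor.

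**What to change.** - State arm + centre + the four-level race/ethnicity stratum (as classified in C.1) as the primary model for Aims 1, 3 and 5.
- Name the same factors, as covariates or strata, for the interval-censored analyses in the addendum.
- In P.2.c, and at the parsimony reference in the Aim 4 text, refer to Aim 1 instead of Aim 2.
- Optionally, add baseline maternal 25(OH)D to the linear Aim 4 models for maternal and cord blood. No centre term needs adding there.

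The cost is about one line of text per model, since every variable is already collected. Three more coefficients are easily carried for Aim 1: at 40 to 50% control incidence and a 25% reduction, 330 × (0.40 + 0.30) = 231 to 330 × (0.50 + 0.375) = 289 events are expected. Aim 5 is thinner, at 435 × (0.10 + 0.05) = 65 events on the Q.5 assumptions. The plan should therefore also say in advance how a very small racial/ethnic group would be pooled.
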